### Follow-up

Transvaginal ultrasonography will be performed 2 weeks after a positive serum or urine pregnancy test to confirm intrauterine pregnancy. Scanning will be repeated later to confirm ongoing pregnancy, which is defined as a viable pregnancy with a foetal heartbeat at 10–12 weeks. Information regarding the outcome of the pregnancy and obstetrical and perinatal complications will be obtained through a review of obstetrical medical records and neonatal medical records. The live birth is defined by the live foetus in the uterine after 20 weeks of gestation.

We will collect the following information within 6 weeks after delivery, including antenatal information (pregnancy complications and foetal information), delivery information (gestational age, mode of delivery, placental weight and birth complications) and newborn information (foetal sex, birth weight and birth defects).

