### Measurement of outcomes

#### Primary outcome

The primary outcome is the live birth rate after 20 weeks of gestation following the fresh transfer.

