#### Secondary outcomes

Secondary outcomes include pregnancy outcomes, maternal safety and obstetric and perinatal complications. Detailed information is provided in Table 2. Maternal safety is an important part of the secondary outcomes. The incidence of OHSS is the key indicator of maternal safety and is classified as mild, moderate or severe according to the RCOG guideline [22, 23]

**Table 2 Tab2:** Secondary outcomes and related definition

Secondary outcomes	Definition
Clinical and laboratory outcomes	
Total amount of FSH	Total amount of FSH used for ovarian stimulation
Number of follicles > 12 mm	The number of follicles > 12 mm measured by transvaginal ultrasound on the day of the trigger or the day before
Number of oocytes obtained	Number of oocytes obtained during oocyte retrieval
Number of embryos obtained	Number and quality of embryos obtained
Proportion of good-quality embryos	Embryos with 4 cells and < 25% fragmentation on day 2 or with ≥6 cells and ≤ 10% fragmentation on day 3, the proportion of oocytes resulting in top quality day 2 (or day 3) embryos according to validated morphological criteria
Oocyte fertilisation rate	The number of zygotes with 2PN over the number of mature oocytes for ICSI or over the number of oocytes for conventional insemination
Endometrial thickness	Endometrial thickness measured by transvaginal ultrasound on the day of the trigger or the day before
Serum E2 level	Serum E2 level on the day of the trigger or the day before
Serum P level	Serum P level on the day of the trigger or the day before
Serum testosterone level	Serum testosterone level on the day of the trigger or the day before
Follicular fluid E2 level	E2 level in the follicular fluid
Follicular fluid testosterone level	Testosterone level in the follicular fluid
Follicular fluid inhibin B level	Inhibin B level in the follicular fluid
Follicular fluid AMH level	AMH level in the follicular fluid
Pregnancy outcomes	
Miscarriage	Spontaneous loss of an intrauterine pregnancy before 20 completed weeks of gestational age
Clinical pregnancy	Presence of one or more intrauterine gestational sacs at 6 weeks of gestation
Ongoing pregnancy	Presence of one or more gestational sacs and foetal heartbeat after 12 weeks of gestation
Maternal safety outcomes	

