### Statistical analysis

#### Sample size calculation

The primary hypothesis of this trial is that the letrozole group will increase the live birth rate when compared with the control group. This treatment will be considered effective if the proportion of women having a live birth is increased by 10% in absolute terms. With an 80% power and a one-sided 2.5% level of statistical significance, we will need to recruit 752 women (376 in each arm) to show an absolute difference of 10% from 35 to 45% between control and letrozole groups. Taking consideration of the dropout rate as 20% (such as cancellation of fresh embryo transfer because of high risk of OHSS), each group will include 450 women (a total of 900 women).

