Missing data will be treated as missing at random and will be imputed using the last observation carried forward (LOCF) method. For the missing values, a sensitivity analysis will be done under the hypothesis of the worst and the best outcomes for each missing individual. Therefore, all secondary outcomes will be considered exploratory. All statistical analyses will be done using the statistical package SPSS (version 26.0, released 2019, IBM corp., Armonk, NY, USA). Statistical significance is defined as *p* < 0.05 with two-sided testing.

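### Missing data are called missing at random but filled by LOCF, which is not a missing-at-random method and is invalid or undefined for a live birth observed once

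*Protocol article*

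**What the plan says.** The missing-data rule is in the protocol article under Statistical analysis, after the sample size calculation: "Missing data will be treated as missing at random and will be imputed using the last observation carried forward (LOCF) method". No outcome is exempted, so it covers the primary one. The next sentence adds that "a sensitivity analysis will be done under the hypothesis of the worst and the best outcomes for each missing individual".

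Under Primary outcome: "The primary outcome is the live birth rate after 20 weeks of gestation following the fresh transfer". The Follow-up section words the event as follows: "The live birth is defined by the live foetus in the uterine after 20 weeks of gestation".

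The pregnancy observations that come before this endpoint are a pregnancy test, a scan ("Transvaginal ultrasonography will be performed 2 weeks after a positive serum or urine pregnancy test to confirm intrauterine pregnancy") and a later scan for ongoing pregnancy, "defined as a viable pregnancy with a foetal heartbeat at 10–12 weeks". Table 2 lists miscarriage as a separate outcome: "Spontaneous loss of an intrauterine pregnancy before 20 completed weeks of gestational age".

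The analysis is by intention to treat. The sample size calculation takes the "dropout rate as 20% (such as cancellation of fresh embryo transfer because of high risk of OHSS").

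**The concern.** Missing at random means that, given what was observed, a missing outcome behaves like the outcomes of comparable women who were followed. Some women seen pregnant will be followed to a miscarriage, so an imputation on that assumption gives a lost pregnant woman a probability of live birth below one. LOCF takes her last state as permanent. The assumption and the method named in the sentence are therefore different things.

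Live birth also has no earlier value of itself to carry. The earlier records are of other outcomes. This is a rule that the protocol states, and states wrongly; it is not detail left to an analysis plan that is not shown. What is at stake is how a woman with an unknown birth outcome enters the primary comparison. Investigators know the allocation in this trial, so that should not be left open until the data are in.

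**Working it through.** **Step 1. The two possible readings, set against the outcome definitions.**
- Carry pregnancy status forward. The test, the first scan and the 10–12 week scan all precede 20 weeks, and Table 2 recognises losses up to then. A woman last seen pregnant before 20 weeks would be counted as a live birth with certainty.
- Carry only the same variable. There is no earlier live-birth value, so nothing is imputed and the stated rule does nothing.

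The article does not say which is meant.

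**Step 2. The plan's own figures.** The plan gives no figure for missing data. The illustration below borrows its 450 women per arm and its rates of 35% and 45%. The plan's sample size for those rates reproduces (pooled variance, one-sided 2.5%, 80% power): (1.960 × √0.48 + 0.842 × √0.475)² / 0.10² = 376 per arm. That figure is not in dispute here.

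**Step 3. Size under the first reading.** Assumptions not in the article: 80% of pregnancies overall end in live birth (used only to get the number of pregnancies); 5% or 10% of pregnancies are lost to follow-up; of those lost, 75–90% end in live birth.

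Pregnancies per arm = 450 × live birth rate / 0.80.
- Control: 450 × 0.35 / 0.80 = 197.
- Letrozole: 450 × 0.45 / 0.80 = 253.

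False live births = pregnancies × share lost × (1 − chance of live birth).
- Control, 5% lost: 197 × 0.05 × 0.10 = 1.0 to 197 × 0.05 × 0.25 = 2.5 women; divided by 450, 0.2 to 0.5 points.
- Control, 10% lost: 2.0 to 4.9 women, 0.4 to 1.1 points.
- Letrozole, 5% lost: 1.3 to 3.2 women, 0.3 to 0.7 points.
- Letrozole, 10% lost: 2.5 to 6.3 women, 0.6 to 1.4 points.

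**Step 4. Effect on the comparison.** With equal loss, most of this cancels. The pregnancy rates differ by (0.45 − 0.35) / 0.80 = 0.125.
- 5% lost: 0.125 × 0.05 × (0.10 to 0.25) = 0.06 to 0.16 points.
- 10% lost: 0.125 × 0.10 × (0.10 to 0.25) = 0.13 to 0.31 points.

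Unequal loss matters more. If 5% of all women in one arm and 2% in the other are lost while pregnant, and 80% of those pregnancies end in live birth, the bias is (0.05 − 0.02) × 0.20 = 0.6 points.

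**Step 5. What the planned best and worst cases do.** Let a share m of each arm be truly missing, with 35% and 45% among the rest. Run in opposite directions by arm, the difference spans 10 × (1 − m) ± 100 × m points.
- m = 2%: 7.8 to 11.8.
- m = 5%: 4.5 to 14.5.

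Run in the same direction in both arms at m = 5%, both cases give 10 × 0.95 = 9.5 points, which bounds nothing. The article does not say which way it will be done.

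**The case against.** Four points can be made for the plan.

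- **The mapping is not stated.** Nothing in the article says that pregnant is to be recorded as live birth. A reader might infer both that LOCF biases the rate upwards and that it has nothing to carry; these belong to different readings and cannot both hold for the same woman. This stands, which is why the point is put as invalid or undefined. Women with a negative test or a miscarriage have a known result, and under the literal definition in the Follow-up section a woman seen with a live foetus after 20 weeks already meets the endpoint. The false conversion is confined to women last seen pregnant before then.
- **Cancelled transfers.** A reader might infer that the 20% called dropout would be treated as missing. Best and worst cases would then run from 0.8 × 0.45 − (0.8 × 0.35 + 0.2) = −12 points to 0.8 × 0.45 + 0.2 − 0.8 × 0.35 = +28 points. The documents do not support this. The word appears only in the sample size inflation, the analysis is by intention to treat, and nothing classes a cancelled transfer as missing. The range is no part of the conclusion.
- **Other variables.** It is tempting to say that LOCF cannot be run for most variables. The Interventions section has scans and serum hormones repeated through stimulation, so serum estradiol and progesterone have earlier values and endometrial thickness may. The objection to LOCF as having nothing to carry is limited to outcomes taken once, such as birth weight and follicular-fluid hormones, and the secondary outcomes are declared exploratory.
- **A sensitivity analysis is planned.** It bounds the effect of truly missing births if run in opposite directions by arm. It leaves LOCF as the main estimate.

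**Conclusion.** The concern holds in this form: the stated rule contradicts itself, and for the primary outcome it is either invalid or undefined, depending on a reading that the article does not settle.

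The likely numerical effect is small. Under the first reading, it is about 0.2–1.1 points on the control arm's rate and, with equal loss, about 0.06–0.3 points on the difference, against a planned 10 points. These figures rest on assumed loss and live-birth shares; the article gives no rate of loss during pregnancy, and unequal loss would enlarge the effect. The case for change is an unworkable primary rule that is cheap to replace. It does not rest on a large demonstrated bias.

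**What to change.** Amend the missing-data paragraph before the analysis:

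1. Delete LOCF for live birth and for outcomes measured once, such as birth weight and follicular-fluid hormones.
2. State that under intention to treat a woman with no fresh transfer, a negative pregnancy test or a miscarriage has an observed outcome of no live birth after fresh transfer and is not missing.
3. Fix one primary rule for births that are truly unknown. One example is to count no documented live birth as none. It is conventional but not free: at 5% of pregnancies lost it removes 197 × 0.05 × (0.75 to 0.90) = 7.4 to 8.9 true births from the control arm (1.6 to 2.0 points) and shrinks the difference by 0.125 × 0.05 × (0.75 to 0.90) = 0.5 to 0.6 points. What matters most is that one rule is fixed in advance.
4. Add, as a sensitivity analysis, multiple imputation under missing at random using arm, centre, age, antral follicle count and last known pregnancy status.
5. Keep the best and worst cases, run in opposite directions by arm and only for women truly lost.

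The cost is wording and a little programming. No new data are needed.

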### Statistical analysis

The result will be analysed according to the intention-to-treat (ITT) principle. Per-protocol (PP) analysis will also be conducted as a sensitivity analysis. Baseline characteristics will be described by descriptive analysis and the balance among groups or subgroups will be assessed by analysis for different kinds of data. For continuous variables, the normality distribution will be estimated by using frequency histograms and the Kolmogorov-Smirnov test initially. If the continuous variables are normally distributed, they will be presented as means with standard deviations (SDs). If the continuous variables are non-normally distributed, their medians and interquartile ranges (IQRs) will be reported. For categorical variables, we will present the proportion between each group. In addition, the recruitment number, those participants lost to follow-up, protocol violations and other relevant data will also be reported. A comparison between groups will be performed using the independent sample *t*-test, Mann-Whitney *U* test for continuous variables or Pearson chi-square test/Fisher’s exact test for categorical variables as appropriate. The primary outcome will be compared using Pearson’s chi-square test or Fisher’s exact test as appropriate. Categorical secondary outcomes will be compared between two groups using a similar approach as the primary outcome. Student’s *t*-test or Wilcoxon test will be used as appropriate for continuous secondary outcomes, such as birth weight, etc. The relative risks (RR) and absolute rate differences (ARD) and their 95% confidence interval (CI) between the two groups will be calculated. And the 99% CI of the ARDs will be used to evaluate if the letrozole group is superior to the control group. Multiple variable logistic regression models will be used to assess the treatment effect adjusting for other potential confounding variables that are unbalanced in the baseline.

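### The planned worst/best-outcome sensitivity analysis does not assign outcomes by arm; read literally, it is a weak check that can miss fragility to missing births

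*Protocol article*

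**What the plan says.** All of this stands in the protocol article. The Primary outcome section makes the endpoint binary: "The primary outcome is the live birth rate after 20 weeks of gestation following the fresh transfer". The Statistical analysis section sets the population: "The result will be analysed according to the intention-to-treat (ITT) principle". It then fixes the main handling of gaps: "Missing data will be treated as missing at random and will be imputed using the last observation carried forward (LOCF) method". The check on that assumption is one sentence: "a sensitivity analysis will be done under the hypothesis of the worst and the best outcomes for each missing individual". The unit named is the individual. The treatment arm is not mentioned, and the text does not define which women count as missing. A per-protocol analysis is also planned as a sensitivity analysis, but it changes the population and does not vary the unknown births.

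The same section judges superiority by the 99% confidence interval of the absolute rate difference and, separately, declares significance at two-sided p<0.05. The Sample size calculation section allows for loss as follows: "Taking consideration of the dropout rate as 20% (such as cancellation of fresh embryo transfer because of high risk of OHSS").

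**The concern.** For a yes/no endpoint, the plain reading of a per-individual rule is that all missing women are set to no live birth, and then all are set to live birth. Both scenarios move the two arms in the same direction, so most of the change cancels in the difference. The trial is open-label, and what could mislead is that women with unknown births fare differently in the two arms. A scenario that treats both arms alike does not vary this.

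The sentence is the only stated check of the primary result against a departure from missing at random. If it is run literally and the losses are balanced, two nearly identical estimates may be presented as evidence of robustness when a modest number of unknown births could overturn the conclusion.

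**Working it through.** **Inputs from the article.** Rates of 35% and 45%; 80% power at one-sided 2.5%; 376 per arm before allowance for loss; 450 per arm randomised 1:1. **Assumed.** The missing counts and the observed counts below.

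**The plan's own figure.** With pooled variance and no continuity correction, n = [1.960·√(2·0.40·0.60) + 0.842·√(0.35·0.65 + 0.45·0.55)]² / 0.10² = (1.358 + 0.580)² / 0.01 ≈ 375.6, so 376 per arm and 752 in total. This agrees with the article.

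**Algebra.** Let rL and rC be the observed live-birth rates and mL and mC the missing shares.
- All worst: D₀ = (1−mL)rL − (1−mC)rC.
- All best: D₁ = D₀ + (mL − mC).
- Opposed, unfavourable to letrozole: D₀ − mC.
- Opposed, favourable to letrozole: D₀ + mL.

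The literal pair therefore spans |mL − mC| and the opposed pair spans mL + mC. With equal shares m, both literal scenarios equal (1−m)(rL − rC).

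**Illustration near the design effect.** Assume 23 missing per arm (23/450 = 5.1%), with observed births 149/427 (34.9%) on control and 192/427 (45.0%) on letrozole. The observed difference is +10.1 points (p=0.003). P-values are Pearson chi-square without correction; intervals are Wald.

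| Scenario | Control | Letrozole | Difference (points) | p | 99% CI |
|---|---|---|---|---|---|
| All worst | 149/450 | 192/450 | +9.6 | 0.003 | +1.3 to +17.8 |
| All best | 172/450 | 215/450 | +9.6 | 0.004 | +1.1 to +18.0 |
| Opposed, against letrozole | 172/450 | 192/450 | +4.4 | 0.17 | −4.0 to +12.9 |
| Opposed, for letrozole | 149/450 | 215/450 | +14.7 | <0.001 | +6.3 to +23.0 |

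Both literal scenarios keep superiority on either stated criterion. The unfavourable opposed scenario loses it on both.

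**How the amount of missing data matters.** Take exact observed rates of 35% and 45%, 450 per arm and equal shares.
- At 2% missing, the literal pair gives +9.8 twice. The opposed pair runs from +7.8 (p=0.017; 99% CI −0.6 to +16.2) to +11.8.
- At 5%, the literal pair gives +9.5 twice. The opposed pair runs from +4.5 (p=0.17) to +14.5.
- At 10%, the literal pair gives +9.0 twice. The opposed pair runs from −1.0 to +19.0.

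The unfavourable opposed scenario loses two-sided 5% significance at about 3.3% missing per arm. It reaches zero where 0.10(1−m) = m, at about 9.1%.

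**Where the literal check does respond.**
- Borderline result, balanced loss: 149/427 against 177/427 has p=0.049. All worst gives p=0.052 and all best p=0.058.
- Unequal loss: 32 control and 14 letrozole women missing, observed about 35% and 42%. All worst gives +8.2 points (p=0.010) and all best +4.2 (p=0.20). The gap is (32−14)/450 = 4.0 points, as the algebra requires.

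**The case against.** The best reply is that the sentence is unspecific rather than wrong. It does not say that both arms receive the same outcome, and a best/worst and worst/best assignment by arm would fit its words. A condensed article may leave that detail to the full protocol or analysis plan, neither of which is shown. This part stands: a reader might infer that the plan rules out opposing the arms, and the text does not support that.

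Three further inferences also go too far.
- That the check cannot fail under balanced missingness. It can, because the difference shrinks by (1−m) and a borderline p-value may cross 0.05, as shown above.
- That the two scenarios always agree. They separate when missing shares differ. If cancelled transfers were counted as missing, that is plausible, since freezing all embryos is advised on estradiol thresholds and letrozole is meant to lower estradiol.
- That 20% of births will be unknown. The 20% is a dropout allowance that names cancelled fresh transfer as an example. The article does not say that such women have a missing birth outcome.

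It is also fair that at 2% missing and a 10-point effect even the unfavourable opposed case keeps p=0.017, though its 99% interval includes zero. Finally, the article promises to report losses to follow-up, so a reader could work out the opposed bounds.

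What remains is that the article does state a rule, and followed literally it never varies outcomes between arms. Even when unequal losses separate the two scenarios, they do so only by the gap in missing shares. If both readings are allowed, the choice between an uninformative pair and a true bound could be made after the data are seen.

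**Conclusion.** The concern holds in a limited form. The sentence leaves assignment by arm open. On its literal reading, it is a weak check that can miss fragility when missing shares are about balanced, and it remains able to fail for a borderline result or when the shares differ. In the illustration it reports +9.6 points twice where the opposed range is +4.4 to +14.7. That rests on 450 per arm, an assumed 23 missing per arm and an observed effect close to the design effect; fewer unknown births would narrow the opposed range. The documents do not support saying that the analysis will declare a fragile result robust, only that it can. The main analysis is not invalidated by this point. The change is worth making before data lock.

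**What to change.** Replace the sentence with two arm-opposed scenarios: missing letrozole women have no live birth while missing control women have one, and then the reverse. Apply them only to women whose birth outcome is truly unknown, and state which women those are, including how a woman with a cancelled fresh transfer is classified.

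Add a tipping-point grid over the assumed live-birth proportion among missing women in each arm. Report where the superiority conclusion changes under the trial's stated superiority criterion, the 99% confidence interval of the absolute rate difference.

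The cost is one sentence and a few lines of code before data lock, with no effect on participants or treatment. The small downside is that the opposed extremes are pessimistic; the grid puts them in context.

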## Discussion

Letrozole is usually used for ovulation induction in anovulatory women and ovarian stimulation and intrauterine insemination for treatment of unexplained infertility. It is now routinely used in women with breast cancer undergoing fertility treatment in order to prevent recurrent breast cancer as a result of supraphysiological estradiol level following ovarian stimulation [14]. Its use in poor responders and normal responders in IVF may reduce the total gonadotropin dose required for ovarian stimulation without increasing the pregnancy rate [24–26]. The hypothesis of the present study is that adding letrozole to gonadotropin in the ovarian stimulation protocol in high responder patients can improve the live birth rate of women with anticipated high ovarian response in IVF. The present study is the first randomised study which provides high-quality evidence about the efficacy of co-administration of letrozole in high ovarian responders and IVF cycles and may open new insights into the clinical management of this group of women.

The strengths of the present study include randomisation, a large adequate sample size to show a 10% absolute difference in the live birth rate between the intervention and control groups and the live birth rate as the primary outcome, which is the most important clinical outcome in fertility treatment studies. Most women prefer to choose embryo transfer in the fresh cycle instead of transfer in frozen cycles because of time constrain, economic reasons and psychological factors, so the use of letrozole during ovarian stimulation for IVF producing a good number of oocytes with physiological levels of estradiol may reduce the adverse impact on endometrial receptivity and increase the success rate of the IVF treatment. To increase the external validity of this trial, we did not limit embryo transfer to day 3 or day 5 only and the results of day 3 and day 5 transfer will be separately analysed. The timing of embryo transfer is unlikely to influence the results because of randomisation in the study.

The limitation is the lack of cumulative live birth rate of the stimulated IVF cycle.

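### Randomisation does not protect the planned separate day 3 and day 5 comparisons, because transfer day and receipt of a fresh transfer are settled after allocation

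*Protocol article*

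**What the plan says.** The Discussion of the protocol article explains that transfer was not restricted to one day, for the sake of external validity, and that "the results of day 3 and day 5 transfer will be separately analysed". The next sentence reads "The timing of embryo transfer is unlikely to influence the results because of randomisation in the study".

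The other relevant statements are these:

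- **Timing.** Table 1 (Study design) places allocation at T1, with ovarian stimulation. Oocyte retrieval (T2), embryo assessment (T3) and transfer (T4) follow.
- **Blinding.** Under Randomisation and allocation concealment, investigators and participants know the allocation; only the biostatistician is blinded.
- **Fresh transfer or freeze-all.** Under Embryo transfer and luteal support, physicians decide according to the woman's condition. Under Interventions, the freeze-all advice is tied to estradiol on the hCG day and to the number of oocytes retrieved.
- **Transfer day.** The same section allows up to two embryos on day 2/3 or one blastocyst on day 5. The article does not say how the day is chosen.
- **Effect of treatment.** The Abstract and Background say that letrozole lowers serum estradiol. Table 2 lists estradiol, oocyte number, and embryo number and quality as secondary outcomes.
- **Main analysis.** The Statistical analysis section uses the intention-to-treat principle and calls all secondary outcomes exploratory.

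**The concern.** Randomisation balances the arms at the moment of allocation. It does not balance them within groups formed afterwards, if treatment can affect who enters each group. Day 3 and day 5 recipients are such groups, and so are women with any fresh transfer, from whom both are drawn.

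The article itself supplies one route for this. Letrozole lowers estradiol, estradiol is a freeze-all criterion, and freeze-all decides who is available for a fresh transfer at all. Embryo number and quality may be a second route, through the choice of day, but the article does not state how that choice is made.

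At stake is the interpretation of the two transfer-day results. A sentence invoking randomisation, placed directly after the plan to split, invites the reader to take a difference within day 3 or day 5 as a treatment effect. It could instead reflect a different mix of women in the two arms.

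**Working it through.** **1. The plan's own figure.** The sample size is set "With an 80% power and a one-sided 2.5% level of statistical significance", for an "absolute difference of 10% from 35 to 45% between control and letrozole groups". With pooled variance under the null and mean rate 0.40:

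n = [1.960 × √(2 × 0.40 × 0.60) + 0.842 × √(0.35 × 0.65 + 0.45 × 0.55)]² / 0.10²
= [1.358 + 0.580]² / 0.01 ≈ 375.6, so 376 per arm.

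This matches the stated 376 per arm (752 in total). It serves here only as the scale: the design target is 10 points.

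**2. Order of events.** Allocation (T1) comes before the estradiol reading on the hCG day, before retrieval (T2), before embryo assessment (T3) and before transfer (T4). Nothing in the article fixes transfer day at allocation. Membership of a day 3 or day 5 group is therefore a post-randomisation variable.

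**3. What can follow within the groups.** The article gives no transfer-day data by arm, so every rate in this step is an assumption. Take two equal prognosis groups with live birth rates of 45% (good) and 25% (poor), so 35% overall, and **no treatment effect**. Freeze-all is set aside, so every woman has a transfer. If day 5 is chosen for a proportion g of good-prognosis and p of poor-prognosis women, then

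- day 5 rate = (g × 0.45 + p × 0.25) / (g + p)
- day 3 rate = [(1 − g) × 0.45 + (1 − p) × 0.25] / (2 − g − p)

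| Day 5 chosen, good/poor: control | Day 5 chosen, good/poor: letrozole | Day 5 rate, control → letrozole | Day 3 rate, control → letrozole | Day 5 difference (points) | Day 3 difference (points) | All women |
|---|---|---|---|---|---|---|
| 60%/40% | 60%/40% | 37.0% → 37.0% | 33.0% → 33.0% | 0 | 0 | 0 |
| 70%/30% | 60%/40% | 39.0% → 37.0% | 31.0% → 33.0% | −2.0 | +2.0 | 0 |
| 70%/10% | 50%/30% | 42.5% → 37.5% | 30.0% → 33.3% | −5.0 | +3.3 | 0 |
| 70%/30% | 50%/10% | 39.0% → 41.7% | 31.0% → 32.1% | +2.7 | +1.1 | 0 |

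For example, in the second row the day 5 control rate is (0.70 × 0.45 + 0.30 × 0.25) / 1.00 = 0.39, and the letrozole rate is (0.60 × 0.45 + 0.40 × 0.25) / 1.00 = 0.37.

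Three things follow:

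- With equal selection in both arms there is no bias. If choice of day is unrelated to prognosis (g = p), both rates are 35% in each arm and again there is none.
- With differential selection related to prognosis, the sign can go either way. In the last row both groups favour letrozole although the true effect is zero.
- The comparison of all women stays at zero in every row.

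**4. Precision of the split.** The planned 450 per arm less the plan's 20% dropout allowance leaves 450 × 0.80 = 360 per arm. The split by day is not given. For 35% against 45% at one-sided 2.5%, power ≈ Φ[(0.10 × √n − 1.358) / 0.689], with n women per arm in the transfer-day group:

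- 30% share, n = 108: about 32%
- 50% share, n = 180: about 49%
- 70% share, n = 252: about 63%

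So the separate comparisons would also be imprecise, quite apart from selection.

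**The case against.** The strongest reply is that the quoted sentence is not about the split. The stated reason for allowing both days is external validity, and the sentence on timing speaks of the results of the study as a whole. Read that way it is largely defensible: transfer day comes after allocation, so it does not confound the comparison of all randomised women. That part stands. The sentence is not an explicit defence of the separate analyses. Even so, transfer day may lie on the path from treatment to birth, so it may influence the overall result as part of the effect. The sentence also still offers no support for comparisons within transfer-day groups.

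The reply can add that the split appears only in the Discussion, that no test or claim is attached to it, and that secondary outcomes are declared exploratory. This limits the consequence but does not remove the selection.

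A reader might infer more than the documents support:

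- **That the transfer-day results will be biased.** Bias needs selection that differs by arm and is related to prognosis. The article shows a route to this, not that it occurs.
- **That the per-protocol analysis has the same fault.** The article says only "Per-protocol (PP) analysis will also be conducted as a sensitivity analysis". It does not define that set. The sample size paragraph counts a cancelled fresh transfer as dropout, but this does not define the per-protocol set either. Women whose embryos are all frozen under the protocol's own rules may well remain in it, and the definition may stand in a document not shown.
- **That the bias can be sized by modelling freeze-all.** Such a model needs assumed links between estradiol, oocyte number and prognosis, and it says nothing about choice of transfer day.

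**Conclusion.** The point holds in a limited form. Comparisons within day 3 or day 5 transfers condition on events after randomisation in an open-label trial, and randomisation does not make the arms comparable there. They can be biased in either direction by an amount that the documents do not reveal. The figures of −5.0 to +3.3 points illustrate what is possible under assumed prognosis and selection rates; they are not an estimate for this trial.

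The primary intention-to-treat result is not biased by transfer day. What is affected is the stated justification and what the trial may conclude from the transfer-day groups.

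**What to change.** 1. Remove the appeal to randomisation, or limit it to the comparison it supports. For example: transfer day is determined after allocation and does not confound the comparison of all randomised women; results by transfer day are descriptive.
2. Present the day 2/3 and day 5 results as descriptive, without causal or confirmatory claims.
3. Add a table by arm, over all randomised women, of the proportions with day 2/3 transfer, day 5 transfer and no fresh transfer. This shows whether the proportions differ by arm. Equal proportions would not by themselves rule out different selection, as the second and third rows of the illustration show.

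The cost is a change of wording and one table. The planned split already requires transfer day to be recorded. The downside is that statements about transfer-day groups in the final report become weaker.
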